### Randomization of participants and concealment

The Stata Ralloc program will generate a randomization sequence by blocks of *n* = 9 and 3 arms per block (A, B and C). In this way, each block of nine pregnant women treated consecutively will be assigned, in a random order, to the arms C (control), I1 (Intervention 1) and I2 (Intervention 2): *C I1 I1 I1 I1 I2 I2 I2 I2*, up to complete the assignment of the 265 pregnant women. The sequence will be generated by the data analysts and kept in the monitoring centre, remaining at all times hidden to those clinicians responsible for the enrolment of pregnant women. Allocation sequence will be concealed until women are assigned to interventions by the research staff/interviewer. This way, the follow-up centre will be contacted each time the interviewer has a pregnant woman, so that they are informed of the arm to which she will be assigned.

There will be concealment for the people in charge of carrying out the evaluation and analysis of the data because they will manage the database without personal women information or knowledge about the group intervention, where women will be allocated. Due to the nature of the study, neither the participants nor the professionals who indicate the intervention can be blinded. Participants will know they will be selected for either a pedometer group or a non-pedometer group. They will not know if the intervention is minimum (pedometer only) or maximum (pedometer and a goal of 11,000 steps/day).

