### Selection criteria for eligibility

Inclusion Criteria: 1) Pregnant women with a minimum of 18 and maximum of 49 years of age; 2) Low medical risk pregnancies that will be attending in the Unit of Obstetrics and Gynecology, in a public third level Maternity Hospital in Granada (Spain); 3) Sedentary women (< 5 days/week of moderate-vigorous physical activity at least > 30 min.; equivalent to < 7000 steps/day); 4) With mobile phone and e-mail; 5) Without intellectual deficits or difficulty to understand the language.

Exclusion Criteria: 1) Chronic disease: diabetes, high-pressure, cardiac or respiratory disease, liver or kidney disease or mobility problems; 2) Women with relative or absolute repose needed; 3) Active women (> 5 days/week of moderate-vigorous physical activity at least > 30 min.; equivalent to > 7000 steps/day); 3) Insomnia at beginning of pregnancy or having drugs for sleep problems.

The study sample will consist of women who, meeting the inclusion criteria, agree to participate, upon request for voluntary collaboration and signing of two documents: 1) Informed consent approved by the Provincial Ethics Committee of Granada and 2) Pedometer loan certificate.

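### One fixed block of nine with a single control, at one open-label site, lets a recruiter who knows the block deduce up to about 16% of exact allocations; random block sizes would cut this cheaply

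*Protocol article*

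**What the plan says.** All of the key statements are in the protocol article under Randomization of participants and concealment.

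- **Block:** "each block of nine pregnant women treated consecutively will be assigned" in random order, with the content "C I1 I1 I1 I1 I2 I2 I2 I2", repeated "up to complete the assignment of the 265 pregnant women". No second block size is described.
- **Custody:** the data analysts generate the sequence and the monitoring centre keeps it, "remaining at all times hidden to those clinicians responsible for the enrolment of pregnant women".
- **Release:** "the follow-up centre will be contacted each time the interviewer has a pregnant woman", and the interviewer is then told that woman's arm. The allocation is "concealed until women are assigned to interventions by the research staff/interviewer".
- **Blinding:** "neither the participants nor the professionals who indicate the intervention can be blinded".

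Selection criteria for eligibility places recruitment in a single public hospital in Granada. Location and data collection says that health staff refer women to a research team member in an adjoining room. It says that recruitment began in June 2019, was paused from March to August 2020, and was to end in December 2020.

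**The concern.** Central, one-at-a-time release protects the list. It does not protect the next allocation from someone who has been told all the previous ones and knows that every nine women contain exactly one control and four of each pedometer arm. That person can subtract what has been used from what the block contains.

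If the next arm is known or partly known, a recruiter can, deliberately or not, influence who enters at that moment, for example by how keen a woman seems to walk. Randomization is meant to exclude this, and a later analysis cannot fully repair it. The bias would act through who enters each arm, so it could touch both primary outcomes, insomnia and steps. The control arm is small (265/9, about 29 women), so each control woman carries about 1/29 = 3.4 percentage points of that arm's insomnia prevalence.

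**Working it through.** The document gives no predictability figure to reproduce. The figures below are for an observer who knows the block content and sees every earlier allocation.

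**Inputs** (Randomization of participants and concealment): block of 9; 1 C, 4 I1, 4 I2; 265 women = 29 full blocks (261 women) plus 4.

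**1. Exact arm certain.** The arm at a given position is certain when all remaining places in the block belong to one arm.
- 9th place: always, 1.
- 8th place: the last two places match, (6 + 6)/36 = 12/36 = 0.333.
- 7th place: the last three match, (4 + 4)/84 = 8/84 = 0.095.
- 6th place: the last four match, (1 + 1)/126 = 2/126 = 0.016.
- Sum: 1.444 per block; 1.444/9 = 16.0%.
- Over the trial: 29 × 1.444 = 41.9. The last four women occupy places 1 to 4 and add none. So about 42 of 265 (simulated 95% range 35 to 50).

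**2. Pedometer versus control certain.**
- Places after the control, averaged over its nine equally likely positions: (0 + 1 + … + 8)/9 = 4.0 per block, or 44.4% of women.
- Control falls last and is therefore known: 1/9 = 0.111 per block.
- Sum: 4.111/9 = 45.7%, about 120 of 265 (simulated mean 119.7, 95% range 95 to 146).

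**3. What that second figure contains.** An upcoming control is certain only when it falls last: (1/9)/9 = 1 in 81 allocations, or 29/9, about 3 women in the trial. With the block known, the best guess of pedometer versus control is wrong once per block unless the control is last: 1 − (8/9)/9 = 73/81 = 90.1%. Always guessing pedometer is right 8/9 = 88.9% of the time. The gain is 1.2 points.

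**4. Best guess of the exact arm.** Taking (largest remaining count)/(places remaining) at each step and averaging over all paths through the block gives 60.4%. Without block knowledge it is 4/9 = 44.4%.

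**5. Effect of undisclosed random block sizes at the same 1:4:4 ratio.** Simulated over 265 women for an observer who knows the possible sizes, equally likely, but not the size in use:

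| Block sizes | Exact arm certain | Pedometer vs control certain | Best guess of arm right |
|---|---|---|---|
| 9 only | 16% | 46% | 60% |
| 9, 18 | 5% | 17% | 58% |
| 9, 18, 27 | 2% | 8% | 56% |

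**The case against.** The strongest reply is that the figures need a recruiter who knows the block and sees every earlier allocation in order, and the document establishes neither. It says that the list is hidden from enrolling clinicians. It does not say that interviewers are told the block structure, or how many of them recruit. Several interviewers who did not share allocations would each foresee less. This stands, and it makes the figures upper bounds. It does not remove the point, because a steady one control in nine can be inferred at a single open-label site.

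A second reply is that discretion is limited: health staff make the referral, consent is signed, and blocks cover consecutive women. This narrows the opportunity but does not close it. Entry also depends on matters that call for some judgement, such as insomnia at the start of pregnancy and understanding of the language.

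A third is that 46% sounds worse than it is. Any woman already has an 89% chance of a pedometer, so learning that the control place has gone moves her only from at most 89% to 100%. This also stands.

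A reader might infer that the printed article itself gave recruiters the block. It describes the 2020 pause as past, and nothing shows that recruiters could read it while enrolling. A reader might also infer that recruiters could readily steer women into or away from control. The 1-in-81 figure and the 1.2-point gain do not support that.

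**Conclusion.** The point holds as a moderate, avoidable weakness in allocation concealment. With one fixed 1:4:4 block of nine, up to about 16% of exact allocations (about 42 of 265) and up to about 46% of pedometer-versus-control allocations could be known beforehand. The second figure comes almost entirely from knowing that the control place is used. Both assume that the recruiter knows or infers the block and sees all earlier allocations.

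It would go too far to say that the comparison is biased. The document shows an opportunity for selection, not that selection took place.

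**What to change.** - **Remaining allocations:** keep the 1:4:4 ratio. After the current block is complete, draw block sizes at random from 9 and 18, or from 9, 18 and 27. Withhold sizes and composition from recruiting staff, including in any document they use.
- **What to expect:** the gain is mainly in removing certainty. Best-guess accuracy falls only from 60% to 58% (or 56%), so this should not be presented as making allocation unpredictable.
- **Women already allocated:** state whether recruiters knew the block structure. Compare baseline characteristics of pedometer women enrolled before the control place in their block with those enrolled after it. Each side averages four women per full block, so 29 × 4 = 116 each if all 29 blocks are complete. A clear difference would suggest selection; the absence of one would not exclude a small effect.
- **Cost:** one regenerated list and slightly looser arm balance over short runs. The baseline check needs only the allocation order and data already collected. If recruitment has closed, only the disclosure and this check remain.

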### Sample size

First, we have carried out the theoretical calculation of the sample size for the definitive study (*n* = 265), based on the following premises: 1) Three study arms: *maximum intervention group*, pedometer + goal + recall (I1): minimum absolute reduction in the prevalence of low compliance with recommendations that are statistically significant to be detected, that it is 15% with respect to I1*; minimum intervention group*, pedometer (I2): minimum absolute reduction in the prevalence of low compliance with recommendations that are statistically significant to be detected, that is 30% with respect to C; and control group (C), with an estimated prevalence of low compliance with physical activity recommendations of 50% [12, 13]. 2) Alpha error: 5%; 3) Power of the study: 80%; 4) Comparison of I1 vs I2: from the previous premises, 120 women would be needed in each arm; Comparison of I1 vs C: from the previous premises, and taking as reference the 120 women of the I1 arm required for the previous comparison, 25 women in the C arm would be required.

A pilot of the previous design was carried out with 72 women not included in this study: 24 women in each arm of the study, interviewed twice (12th and 20th GW), during the months of February to May 2018. The recruitment period was 3 months. To select a total of 265 women, 1 year and 7 months would be required (considering holiday periods and Covid-19). We estimate 20–30% of losses in second and third interviews (due to neonatal loss or abandonment of the study).

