Finally, a bivariate mixed-effects logistic regression model will be carried out to determine which variables influence the greater frequency of insomnia, considering the latter quantitatively. To delimit the extent to which the associations that appear are explainable by the effect of the rest of the variables included in the study, a multivariate mixed-effects logistic regression model will be constructed. 95% confidence intervals (CI) will be obtained. All contrasts will be bilateral and statistical significance will be considered when the *p* value is ≤0.05. The data analysis will be carried out by intention to process and by protocol, using the Stata / SE v15.0 statistical package.

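### The 4:4:1 blocks of nine split 265 women about 118/118/29, not the 120/120/25 of the sample size calculation: a small mismatch, fixed by restating the figures

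*Protocol article*

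**What the plan says.** The Sample size section of the protocol article sets a 5% alpha and 80% power. For I1 v I2 it concludes that "120 women would be needed in each arm". For I1 v control it continues: "taking as reference the 120 women of the I1 arm required for the previous comparison, 25 women in the C arm would be required". The three arm sizes add up to the stated total of 265.

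The section on randomization and concealment describes fixed blocks: "each block of nine pregnant women treated consecutively will be assigned, in a random order". The content of a block is "C I1 I1 I1 I1 I2 I2 I2 I2", that is, one control, four I1 and four I2. Blocks are used "up to complete the assignment of the 265 pregnant women".

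**The concern.** The two sections give different designs for the same 265 women. The sample size implies 120:120:25, or 4.8:4.8:1, while the blocks implement 4:4:1. The total of 265 is also not a multiple of nine, so the last block is incomplete. The stated arm sizes are the ones to which the 80% power is attached. If the randomization cannot produce them, the power statement describes a trial that will not be run. The comparison to check is I1 v I2, because the blocks give the pedometer arms a smaller share of the women than the calculation assumes.

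**Working it through.** **Inputs.** From Sample size: total 265; 120 in each of I1 and I2; 25 in C; alpha 5%; power 80%; 50% low compliance in C. From the randomization section: blocks of nine with C:I1:I2 = 1:4:4. From Data analysis: two-sided tests ("All contrasts will be bilateral").

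**Assumptions.** Every block has the listed content, and one sequence is used in order up to woman 265. The effect-size wording is unclear. The most coherent reading is low compliance of 50% in C, 35% in I2 and 20% in I1, and it is used below as an assumption.

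**1. The plan's own figures.**
- Total: 120 + 120 + 25 = 265, which agrees.
- Controls: with 20% v 50%, 120 women in I1 and unpooled variances, n_C = 0.25 / [(0.30/2.80)² − 0.16/120] = 24.7, so 25. This agrees.
- Pedometer arms: with 35% v 20%, two-sided, the requirement is 136 (unpooled) or 138 (pooled) per arm, not 120. A two-sided 30% v 15% gives 121. The 80% at 120 per arm is therefore taken at face value in step 3 and not confirmed.

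**2. What the blocks deliver.**
- 265/9 = 29.44, so there are 29 full blocks and a partial one.
- 29 full blocks hold 261 women: 29 C, 116 I1, 116 I2.
- The last 4 women come from a block containing a single C, so they add 0 or 1 control and 4 or 3 pedometer women.
- Hence C = 29 or 30, and I1 + I2 = 236 or 235. Two arms of 120 need 240.
- Expected sizes: 265 × 4/9 = 117.8 in each pedometer arm and 265/9 = 29.4 controls.
- Either pedometer arm can lie between 116 and 120, but one reaches 120 only if the other stays at 116. The probability that both reach 120 is 0, and the probability of at least 25 controls is 1.

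| | I1 | I2 | C |
|---|---|---|---|
| Sample size section | 120 | 120 | 25 |
| Block scheme, expected | 117.8 | 117.8 | 29.4 |
| Block scheme, possible | 116–120 | 116–120 | 29–30 |

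**3. Power, I1 v I2.** Accepting 80% at 120 per arm, power at n per arm is Φ(2.80 × √(n/120) − 1.96). At n = 118 this is Φ(2.80 × 0.9916 − 1.96) = Φ(0.817) = 79.3%. Direct two-proportion calculations (pooled, two-sided) show a change of similar size: 79.8% to 79.2% for 30% v 15%, and 74.3% to 73.5% for 35% v 20%.

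**4. Power, I1 v C, for 20% v 50%.** Power is Φ[(0.30 − 1.96 × SE₀)/SE₁], where SE₀ uses the pooled proportion and SE₁ the separate ones.
- 120 v 25: SE₀ = 0.0954, SE₁ = 0.1065, so Φ(1.06) = 85.6%.
- 118 v 29: SE₀ = 0.0908, SE₁ = 0.0999, so Φ(1.22) = 88.9%.

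All these figures are before losses.

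**The case against.** The best reply is that nothing turns on two women per arm. The shortfall is 2/120, or under 2%, and it moves power by less than one point. The plan itself expects 20–30% losses, which would take 118 per arm to about 94 to 83 and swamp this difference. That stands as a judgement of size. It does not remove the contradiction, because the article states both the arm sizes and the exact block content, and the two cannot both hold.

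Three stronger readings are tempting, and the article supports none of them.

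- A reader might infer that the control requirement is also missed. The text says that "25 women in the C arm would be required", which is a minimum for power. Every possible sequence gives 29 or 30, which is 16–20% more, and the control comparison gains.
- A reader might infer that precision figures against control rest on the wrong number. The article reports no such figures, only the requirement of 25.
- A reader might conclude that the 80% is lost because of the block ratio. The ratio accounts for under one point. Whether 120 per arm gives 80% at all depends on how the effect sizes are read, which is a separate question.

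**Conclusion.** The point holds as a minor inconsistency. The blocks described will give about 118/118/29. Controls exceed their requirement, and the two pedometer arms together fall 4 or 5 women short of 240. The arm sizes are certain, given the stated block content and a total of 265. The power figures are conditional. The fall from 80% to 79.3% for I1 v I2 accepts the plan's own 80% at 120 per arm. The rise from about 86% to 89% for I1 v control assumes 20% v 50% and a two-sided normal approximation. Neither changes what the trial can conclude.

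**What to change.** In the Sample size section, keep 120/120/25 as the calculated requirement, but add that 4:4:1 blocks of nine give expected arm sizes of about 118/118/29 for 265 women. Restate the power for I1 v I2 and I1 v control at those sizes. The cost is a few sentences and a slightly less favourable figure for I1 v I2; no extra women are needed.

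The allocation ratio should not be changed mid-trial. Blocks in the ratio 24:24:5 would match 120/120/25 from the start, since 5 × 53 = 265, but recruitment began in June 2019 and a late switch would not restore those sizes. For illustration, suppose 135 women were already assigned as 60/60/15. The remaining 130 would add about 59/59/12, giving about 119/119/27. The switch would also tie arm proportions to calendar period, around the recruitment pause of March to August 2020.

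If the sponsor wants 120 in both pedometer arms, 30 complete blocks (270 women) give 120/120/30 with the present ratio and five more women. The size of the shortfall does not require this.

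### Analysts said to be blind to group also generate the allocation sequence, de-identification cannot hide control status, and blinding of those who collect the insomnia outcome is not secured

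*Protocol article*

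**What the plan says.** All of the blinding text is in the protocol article, section Randomization of participants and concealment.

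- **Who makes the list:** "The sequence will be generated by the data analysts and kept in the monitoring centre".
- **From whom it is hidden:** "remaining at all times hidden to those clinicians responsible for the enrolment of pregnant women". No one else is named.
- **Who assigns:** "Allocation sequence will be concealed until women are assigned to interventions by the research staff/interviewer", and "the follow-up centre will be contacted each time the interviewer has a pregnant woman, so that they are informed of the arm".
- **Who is said to be blind:** "There will be concealment for the people in charge of carrying out the evaluation and analysis of the data". The reason given is that "they will manage the database without personal women information or knowledge about the group intervention".
- **Who is said not to be blind:** "neither the participants nor the professionals who indicate the intervention can be blinded". On the two pedometer arms, women are told less: "They will not know if the intervention is minimum (pedometer only) or maximum".

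Other sections bear on this. Location and data collection has trained staff conduct three interviews. Instruments places the AIS, the Pittsburgh index (PSQI) and the pregnancy symptom inventory (PSI) in a face-to-face structured interview, and takes average sleep hours from the wrist device. The Abstract limits step measurement to I1 and I2, and Arms and interventions gives the control arm no pedometer.

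**The concern.** A reader will take the blinding statement as a safeguard on the analysis. Such a safeguard would matter here because the article leaves influential choices open. Outcome measures allows insomnia to be an AIS score of at least 6 (stated sensitivity 93%, specificity 85%) or at least 7 (84%, 90%), and these two rules classify different women. Data analysis makes the choice between parametric and non-parametric tests depend on the data, and plans both an intention-to-treat and a per-protocol analysis. An analyst who knows the groups could settle such points with the results by arm in view.

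The other risk is at data collection. The AIS is self-reported by women who know whether they wear a device, and it is asked in person. If the person asking also knows the arm, that is a second route by which expectation could reach a primary outcome.

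**Working it through.** The plan gives no figure for blinding, so there is none to reproduce. The check sets the statements side by side and does the allocation arithmetic.

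**1. Analysts and the sequence.** One paragraph has the data analysts create the list; the next says those analysing the data lack knowledge of group. The text describes no second statistician and no separate code-holder. Storing the list at the monitoring centre does not undo its having been generated by the analysts. Blocks are filled by women seen consecutively. Someone with the list and the order of enrolment could therefore assign all three arms, including I1 versus I2. Whether enrolment order or interview dates stay in the analysis file is not stated, so this is a possibility and not a fact.

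**2. Arm sizes.** Inputs from the same section: 265 women, and blocks of 9 with 1 control, 4 I1 and 4 I2.

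- 265 / 9 = 29.4, so 29 full blocks, covering 29 × 9 = 261 women.
- Full blocks give 29 × 1 = 29 controls and 29 × 4 = 116 in each of I1 and I2.
- The remaining 265 − 261 = 4 women include 0 or 1 control and 0 to 4 from either pedometer arm.
- Result: 29 to 30 controls, and 116 to 120 in each pedometer arm.

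Losses do not blur this. Sample size expects 20–30%. In an extreme case with 30% lost from a pedometer arm and none from control, 116 × 0.70 = 81 remain against 30. Control is identifiable from its size under any code.

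**3. Data fields.** Steps and device-measured sleep exist for I1 and I2 and cannot exist for control. Removing names and contact details leaves these fields in place.

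**4. What the data do not show.** I1 and I2 have equal block shares and the same fields. Size and missingness therefore sort women into two classes, pedometer and control, and not into three arms. For the roughly 265 × 8/9 = 236 women with a device, the file alone does not say which arm is which. Higher steps in one coded group may suggest it, since that is the difference the trial expects.

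**5. Outcome collection.** The interviewer is told the arm when the woman is assigned. The AIS is obtained in an interview by trained staff. No assessor kept unaware of the arm is described for 32 weeks, and nothing says whether the staff who assign also conduct the later interviews.

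**The case against.** The strongest reply has four parts.

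- **Making a list is not the same as holding each record's arm.** The list is kept elsewhere, the analysts receive a de-identified file, and the text does not say that the same individuals generate the list and run the analysis. A condensed article may leave that separation to the full protocol. This is a reason not to call the blinding non-existent. It does not remove the contradiction, because the article gives the task to the analysts in so many words.
- **Data evaluation may mean database handling, not interviewing.** That reading is open, and those who deliver the intervention are already declared unblinded. What stands is that no blinded collection of the insomnia outcome is described, and that the wording invites readers to assume one.
- **The open analysis choices may be settled in a statistical analysis plan that is not shown.** This is possible. The two AIS cut-offs are nonetheless stated as alternatives in the article, and one sentence would close that choice.
- **Changing procedures in mid-trial has costs.** Recruitment began in June 2019. Switching the AIS and PSQI from interview to self-completion now would mix modes for a primary outcome, so that remedy should not be used.

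A reader might go further and infer that every woman's arm can be read from the data, or that the 32-week interviewers are known to be unblinded. The documents support neither. The first holds only for control versus pedometer, and the second is not stated either way.

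**Conclusion.** The point holds as an internal contradiction and an undelivered safeguard. Analyst blinding is contradicted by the article's own account of who generates the sequence. Removing personal information cannot mask control status, which is visible from device-only fields and from 29–30 against 116–120 women. I1 versus I2 is recoverable only through the sequence, or suggested by step counts. Assessor blinding is not secured, although it is not shown to be absent.

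The arm sizes assume that blocks are filled as described up to 265 women. Recovery of I1 versus I2 assumes that enrolment order or dates can be linked to the list. No numerical bias in the insomnia comparison can be derived from the document. The matter should be put right, because the remedy is cheap and protects a primary outcome whose cut-off is still open.

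**What to change.** 1. Have a person who takes no part in the analysis hold the existing list and generate any further sequence. This cannot undo what the analysts may already know, so the next step carries most of the protection.
2. Before real codes are merged, fix one AIS cut-off (6 or 7). Finalise the insomnia, PSQI and PSI code on a file with dummy allocation and no device variables. Code the step analysis separately under dummy I1/I2 labels, since steps are themselves a primary outcome and cannot be left out.
3. Correct the blinding statement to say that control status cannot be masked from the analysts, who generates and who holds the sequence, who collects the insomnia outcome, and whether those interviewers know the arm.
4. Leave the interview mode of the AIS and PSQI as it is.

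The cost is one reassigned task, a little extra data management to prepare the dummy files, and a weaker but accurate blinding statement. No extra participants or visits are needed.
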